### Outcome Measures

#### List of Outcome Measures

The primary outcome measure of the Phase III trial will be child TSE as assessed by hair nicotine.

Secondary outcome measures are:

1. Child TSE, as assessed by parental report

2. Adoption of voluntary smoking bans in homes and cars

3. Risk perception, attitudes and knowledge regarding child TSE

4. All child respiratory symptoms, including sneezing, wheezing, coughing, sore throat, and ear infections, as reported by the parents.

5. Parental smoking cessation, number of parental quit attempts, use of cessation medications, attendance at behavioral cessation sessions

#### Measurement

##### Measurement of TSE

• Hair nicotine levels. Hair will be cut at the scalp prior to and 3-6 months after the intervention. Several centimeters of several hairs will be taken from hair at the scalp. The proximal 1 cm of hair represents exposure during the previous month.

• Parental report of child TSE, obtained through questionnaires, including information on frequency of regular exposure, smoking habits of both parents, smoking bans in house and car, smoking behavior of frequent and occasional visitors; exposure to regular smoking elsewhere (such as in daycare or at grandparent).

##### Justification of choice of TSE measures

The measurement problem is a difficult one, and deficiencies in measurement, whether due to poor sensitivity or bias, may be a contributor to the mediocre results often observed in previous programs. If the measures used are not sensitive enough to detect small differences, then the "noise" in the measurements will obscure being able to document true effects of an intervention. If the measures are biased, and that bias is affected by intervention group (for example, with parental report), then spurious effects may be observed.

There are two approaches to measurement of child TSE: parental report and biochemical measurement. Neither method is perfect: parental report may be compromised by lack of knowledge of child exposure, lack of awareness of that exposure, or social desirability bias. The most widely accepted measure of parentally-reported exposure is number of cigarettes to which the child is exposed. In our early piloting of questionnaires, this measure proved difficult for parents to answer.

Several past studies found parental report to be sufficient [52-54], while other studies showed parents underreported exposure [55] or that such reports were unreliable [56]. In 2006, the US Surgeon General recommended use of biomarkers, particularly cotinine for assessment of SHS exposure [2]. The recent Cochrane 2006 review of programs to reduce children's exposure to SHS [4] stated "We take biological verification of exposure to or absorption of ETS [Environmental Tobacco Smoke] as the "gold standard", and recommended the use of hair nicotine for estimation of long-term exposure.

One review examined reported correlations between biochemical measures and parental report from a number of studies, and found that correlations between parental report and nicotine ranged from .22 - .75, while correlations between parental report and cotinine ranged from .28 - .71 [52] While this may be sufficiently accurate to differentiate between children of smokers and non smokers, it may not be accurate enough to detect differences in levels of exposure obtainable by intervention programs.

Our decision to use hair samples was based primarily on the higher precision of hair nicotine found in the literature [57]. Logistical considerations were also important, as the samples need to be shipped internationally for analysis, and transport delays of biologically perishable samples could result in loss of data. Indeed, a report of a very recent study includes measurement of exposure using hair nicotine [51], perhaps for similar reasons to ours.

### Statistical Considerations

#### Statistical analysis

The Phase I and II results will be analyzed primarily through descriptive methods. In the Phase III trial, the effectiveness of the intervention on hair nicotine level and parental report of child TSE will be analyzed using linear mixed models, which will take into account dependencies in the dataset due to within-clinic correlations between parents. Clinic will be included as a random effect. Baseline hair nicotine level will be included as a covariate. Potential confounding variables relating to socioeconomic status, ethnicity, and religiosity, as ascertained from the initial parental interview, will be included as covariates.

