#### Sample size calculation for the Phase III trial

The final sample size calculations for the Phase III trial will be based on results from the Phase II pilot study. Preliminary calculations have been made on the basis of published data for hair cotinine, and hair nicotine [58,59]. These calculations are based on a power of 0.8 and a 2-sided alpha-level of 0.05. The published data we have used are population or sample level data on levels of hair cotinine in children exposed or not exposed to SHS, or on levels of hair nicotine in children whose parents smoke in the house, smoke only outside the house, or do not smoke at all. We made the following assumptions:

a. The aspirational goal is elimination of TSE among the children. However, our more realistic, operative goal, on which sample size calculations were performed, is a *reduction *in exposure. We define a detectable change of substantive importance as one which produces a change in exposure equivalent to one third the difference in measured hair values between children exposed and unexposed to tobacco smoke.

b. There will be some leakage of the intervention to the control group, as a direct result of the recruitment process. This is consistent with the improvements seen in twelve out of eighteen trials in the control groups, of studies included for review in the Cochrane systematic review [4]. We assume that this contamination will occur in 10% of the recruited children in the control group. This number is based on observed changes in a previous health intervention trial which was run by two of the authors of the present study [39]. Thus, the expected outcome in the control group is a weighted average of the values for exposed children (90%) and the expected change as a result of the intervention (10%).

c. An Inflation Factor (IF) is necessary to compute sample sizes due to the possibility that some of the variance is due to similarities within children attending the same clinic. The inflation factor we used is 1.145.

d. We further assume that 20% of the children recruited will be lost to follow-up.

Based on our tentative calculations, a total of eighteen clinics will be randomized equally to intervention and control groups. Thirty children will be recruited from each clinic. Five hundred and forty infants will be recruited to the study.

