##### Sample size formula

The total sample size is calculated by the following standard formula: [60]

Here z_a _= 1.96 and z_b _= 1.28, for 90% power at the two-sided 0.05 level, Δ is the relevant effect size, and σ is the relevant standard deviation (SD). The sample size is then multiplied by the Inflation Factor (IF) and divided by the expected response rate of 0.8.

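### The parental-report outcome is adjusted for baseline hair nicotine and not, as written, for baseline parental report, so precision on this secondary outcome is likely lost

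*Protocol article*

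**What the plan says.** The primary outcome of the Phase III trial is hair nicotine. The first secondary outcome under List of Outcome Measures is "Child TSE, as assessed by parental report".

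The Statistical analysis section treats both together: "the effectiveness of the intervention on hair nicotine level and parental report of child TSE will be analyzed using linear mixed models". Clinic is a random effect. On baseline exposure the section has one sentence: "Baseline hair nicotine level will be included as a covariate". The remaining covariates are demographic: "Potential confounding variables relating to socioeconomic status, ethnicity, and religiosity, as ascertained from the initial parental interview, will be included as covariates". No section names baseline parental report as a covariate.

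Two other places bear on the point. Justification of choice of TSE measures reports, from a review of several studies, that "correlations between parental report and nicotine ranged from .22 - .75"; it does not say whether the nicotine was measured in hair. Measurement of TSE gives before-and-after timing for the hair samples, but for the report it says only "Parental report of child TSE, obtained through questionnaires" and lists the topics, without time points.

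**The concern.** In a model for a follow-up measurement, the baseline value of the same measurement is usually the strongest single predictor of the outcome. For hair nicotine the section follows that practice. For parental report, read as written, it uses the baseline of a different measure, whose agreement with parental report the article itself describes as variable and possibly too low to detect the differences that such programs achieve.

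If baseline hair nicotine explains little of the follow-up report, the standard error of the intervention effect on this outcome is larger than it need be. A real effect on the first-listed secondary outcome could then be missed, although the children and the interviews are already in the design.

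**Working it through.** **Does the plan's sample size depend on this?** No. With Δ = ln[(1 − 0.1R)/(1 − R)] and R = 0.33, Δ = 0.3669. Total N = 4 × (1.96 + 1.28)² × 1.00² / 0.3669² × 1.145 / 0.8 = 446.4, which rounds up to the 450 in Table 3. The inputs are the SD of log hair nicotine, the inflation factor and the response rate. Neither parental report nor any baseline adjustment enters, so no stated figure changes. (The calculation reproduces with "for 90% power at the two-sided 0.05 level". The power of 0.8 given in the opening paragraph of the sample size section does not reproduce it. That is a separate matter.)

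**Inputs for the comparison**
- c, correlation of parental report with nicotine at the same time: .22 to .75, from Justification of choice of TSE measures, used here as if it applied to hair.
- r, correlation of baseline with follow-up report: not in the document; assumed 0.5 to 0.7.
- x, correlation of baseline hair nicotine with follow-up report: not in the document; it needs a further assumption, varied below.

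**Formulas.** Residual variance as a share of outcome variance:
- hair nicotine only: 1 − x²
- baseline report only: 1 − r²
- both: 1 − (r² + x² − 2rxc)/(1 − c²)

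**Case A: hair predicts later report only through baseline report, x = c × r.** Hair then adds nothing once baseline report is in the model, so using both gives the same result as report alone.

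| c | r | x | Hair only | Report added | Variance | Standard error |
|---|---|---|---|---|---|---|
| .22 | 0.5 | 0.110 | 0.988 | 0.750 | −24% | −13% |
| .22 | 0.7 | 0.154 | 0.976 | 0.510 | −48% | −28% |
| .75 | 0.5 | 0.375 | 0.859 | 0.750 | −13% | −7% |
| .75 | 0.7 | 0.525 | 0.724 | 0.510 | −30% | −16% |

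As an illustration, take 540 × 0.8 / 1.145 / 2 = 188.6 effective children per arm and an assumed standardised effect of 0.25. Power then rises, in row order, from about 69% to 80%, 69% to 93%, 75% to 80% and 81% to 93%.

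**Case B: hair and report are both noisy measures of one true exposure with independent errors.** Then x = c × r / reliability of the report. With c = .75, r = 0.5 and an assumed reliability of 0.7, x = 0.375 / 0.7 = 0.536.
- Hair only: 1 − 0.287 = 0.713.
- Report only: 0.750, which is worse than hair.
- Both: 1 − (0.250 + 0.287 − 0.402)/0.4375 = 0.691, about 3% below hair only.

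**Case C, an extreme: the .75 persists undiminished to follow-up, x = .75, with r = 0.5.**
- Hair only: 1 − 0.5625 = 0.4375.
- Report only: 0.750, a standard error 31% higher (√(0.750/0.4375) = 1.31).
- Both: 1 − (0.250 + 0.5625 − 0.5625)/0.4375 = 0.429, about 2% below hair only.

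Swapping one baseline for the other can therefore help or harm. Adding baseline report lowers residual variance in every case shown, by amounts from 2% to 48%. None of these figures allows for variance already explained by the demographic covariates.

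**The case against.** The strongest reply is that the section is a condensed account and never excludes baseline report. The covariate sentence may be meant for the primary outcome only, and the full covariate list of a secondary model is often left to an analysis plan. It stands that a reader should not infer a deliberate decision against baseline report; the text does not show one. But this is not mere silence. The sentence follows directly on one naming both outcomes and fixes a covariate without limiting it to either, so an analyst following it would fit hair nicotine to both.

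Three further objections stand and limit the point.
- **Size.** A reader might take 13% to 48% as the expected gain. The document gives neither r nor x, and its .22 to .75 is not tied to hair. Cases B and C show the gain nearly vanishing. At the upper end of that range, hair nicotine is not a weak proxy.
- **Bias.** A reader might infer that adjusting for baseline report protects against reporting bias. The article's worry is bias that differs by intervention group, which arises after baseline and which no baseline covariate removes. Stable differences between parents in how they report are, under randomisation, noise or chance imbalance.
- **Availability.** A reader might infer that baseline report is certainly at hand. The section ties the initial interview to socioeconomic status, ethnicity and religiosity, and the questionnaires have no stated time points. Baseline exposure questions are implied, not stated.

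**Conclusion.** The point holds as one of efficiency and clear specification for a secondary outcome. On its plain reading, the plan adjusts parental report for another measure's baseline and omits its own, and precision is likely lost. The loss is about 13% to 48% of residual variance (7% to 28% of the standard error) if hair nicotine predicts later report only through baseline report and r is 0.5 to 0.7. It is smaller under other assumptions, at 2% to 3% in the two examined.

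The stronger reading, that the parental-report analysis is invalid or biased, is not supported: randomisation keeps the treatment estimate valid with either covariate. Nor do the documents support dropping hair nicotine from that model, since doing so could raise the standard error. The primary analysis and the sample size stand as they are.

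**What to change.** In the Statistical analysis section, state which baseline covariate belongs to which outcome:
- Hair nicotine model: log baseline hair nicotine, matching the log scale used for the endpoint in the sample size section.
- Parental-report model: baseline parental report, with baseline hair nicotine kept as an additional covariate.

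In Measurement of TSE, state that the exposure items used for the report outcome are asked at the initial parental interview as well as at follow-up, in the same form.

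The cost is two sentences and one extra covariate in a secondary model, which is negligible with several hundred children. If the exposure items are not already in the initial interview, a few questions are added to a contact that is planned anyway.

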#### Sample size calculation for the Phase III trial

The final sample size calculations for the Phase III trial will be based on results from the Phase II pilot study. Preliminary calculations have been made on the basis of published data for hair cotinine, and hair nicotine [58,59]. These calculations are based on a power of 0.8 and a 2-sided alpha-level of 0.05. The published data we have used are population or sample level data on levels of hair cotinine in children exposed or not exposed to SHS, or on levels of hair nicotine in children whose parents smoke in the house, smoke only outside the house, or do not smoke at all. We made the following assumptions:

a. The aspirational goal is elimination of TSE among the children. However, our more realistic, operative goal, on which sample size calculations were performed, is a *reduction *in exposure. We define a detectable change of substantive importance as one which produces a change in exposure equivalent to one third the difference in measured hair values between children exposed and unexposed to tobacco smoke.

b. There will be some leakage of the intervention to the control group, as a direct result of the recruitment process. This is consistent with the improvements seen in twelve out of eighteen trials in the control groups, of studies included for review in the Cochrane systematic review [4]. We assume that this contamination will occur in 10% of the recruited children in the control group. This number is based on observed changes in a previous health intervention trial which was run by two of the authors of the present study [39]. Thus, the expected outcome in the control group is a weighted average of the values for exposed children (90%) and the expected change as a result of the intervention (10%).

c. An Inflation Factor (IF) is necessary to compute sample sizes due to the possibility that some of the variance is due to similarities within children attending the same clinic. The inflation factor we used is 1.145.

d. We further assume that 20% of the children recruited will be lost to follow-up.

Based on our tentative calculations, a total of eighteen clinics will be randomized equally to intervention and control groups. Thirty children will be recruited from each clinic. Five hundred and forty infants will be recruited to the study.

We assume that treatment is allocated at the clinic level, with the same number of clinics in each of the two arms. The sample size calculations are based on (1) published descriptive statistics for hair nicotine and hair cotinine, (2) specified effect sizes, (3) a projected average clinic size of 30 infants, and (4) a projected response rate of 80%. The sample sizes are also adjusted using an inflation factor to account for the correlation between children attending the same clinic.

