##### Specification of the effect size

The effect of SHS can be expressed as the ratio of the hair nicotine or cotinine level between exposed and unexposed populations. We assume that the program will reduce this ratio by 25%, 33%, or 50%. We further assume that, due to leakage of the program to the control group, the ratio will be reduced in the control group by an amount equal to 10% of the reduction in the treated group (i.e. 2.5%, 3.3%, or 5%).

We perform the calculations on a logarithmic scale. Denote by R the reduction achieved by the program. The effect size (i.e. difference between treatment groups) on the logarithmic scale is then given by

For R = 0.25, 0.33, and 0.50, the corresponding Δ values are Δ = 0.26, 0.37, and 0.64.

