##### Estimation of the Inflation Factor (IF)

The IF is determined by the intraclass correlation coefficient (ICC) and the number of children per clinic [61]. The formula is IF = (1+(m-1)ρ), where m is the average number of children per clinic and ρ is the ICC. As was done by the authors of a previous study, we assume ρ = 0.005. Our assumed clinic size is m = 30. Hence the IF is given by IF = 1+29*0.005 = 1.145.

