##### Estimation of the standard deviation (SD)

###### Hair Nicotine

Our endpoint is log hair nicotine level. Al-Deleimy et al. [59] presented geometric means and associated confidence intervals for hair nicotine. These results were generated by computing arithmetic means and associated confidence intervals for log hair nicotine and then backtransforming to the original hair nicotine scale. From the results presented in the Al-Deleimy paper, we can derive the SD for log hair nicotine in the Al-Deleimy study.

Al-Deleimy et al. presented data for nonsmoking families, parents who smoked only outside the house, and parents who smoked inside the house as well as outside. Table 2 presents the published results and the corresponding SD's for log hair nicotine. Given the above results, we estimate the SD for log hair nicotine at σ = 1.00.

**Table 2 T2:** Hair Nicotine Results From Al-Deleimy et al

	Published N	Published Geometric Mean	Published Confidence Interval	SD for Log Hair Nicotine
No exposure	101	0.58	[0.49,0.68]	0.84
Smoke outside the house	69	2.63	[2.03,3.40]	1.09
Smoke inside the house	127	5.62	[4.60,6.86]	1.15

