###### Hair Cotinine

Florescu et al. [58] presented descriptive statistics for hair cotinine for various populations. We focus on the population of children, either exposed or unexposed to tobacco smoke.

Florescu et al. state on page 440 of their paper that hair cotinine did not follow a normal distribution, and they therefore presented geometric means and some other statistics of interest. We take log hair cotinine as our endpoint, and assume that it is normally distributed. From standard mathematical results for the lognormal distribution, we can use the results in the Florescu et al paper to calculate estimates of the mean and SD of log hair cotinine.

The estimated means for log hair cotinine are in close agreement with the reported geometric means for hair cotinine previously reported [exp(-1.59) = 0.20 vs. 0.19, exp(-0.84) = 0.42 vs. 0.48]. Based on the results, we estimate the SD for log hair cotinine at σ = 1.15.

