##### Calculated Sample Size

Given the foregoing development, the calculated total sample sizes for log hair nicotine and log hair cotinine at the various levels of R are as follows (rounded up to the nearest 10) as seen in Table 3.

**Table 3 T3:** Calculated Total Sample Sizes

	Log Hair Nicotine	Log Hair Cotinine
R = 0.25	880	1,160

R = 0.33	450	600

R = 0.50	150	200

The calculated sample sizes are higher for log hair cotinine than for log hair nicotine. This is consistent with the claims that hair nicotine is more sensitive than hair cotinine.

Using R = 0.33 and taking log hair nicotine as the endpoint, we get a total sample size of 450 infants. Since the number of infants has to be an even multiple of the clinic size, which we are assuming is 30, we get a total sample size of 480. We increase this to 540 infants as a security measure against possible clinic dropout and the uncertainty in the estimates used. We thus set the tentative total sample size at 540 infants (9 clinics in each of the two arms, with 30 infants per clinic). The final choice of endpoint and sample size will be made on the basis of locally-collected data.

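### The protocol gives two powers, 0.8 and 90%, for the same sample size calculation; Table 3 follows from 90%, so the 0.8 is wrong as written and could cut the post-pilot recalculation by a quarter

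*Protocol article*

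**What the plan says.** In the protocol article, under Statistical Considerations, the section on the Phase III sample size opens by describing the preliminary calculations: "These calculations are based on a power of 0.8 and a 2-sided alpha-level of 0.05".

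The subsection Sample size formula then sets the quantiles at 1.96 and 1.28, "for 90% power at the two-sided 0.05 level". The result is multiplied by the inflation factor and divided by a response rate of 0.8.

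The subsection Calculated Sample Size gives Table 3 and takes one entry forward: "Using R = 0.33 and taking log hair nicotine as the endpoint, we get a total sample size of 450 infants". That figure is raised to 480 to fit clinics of 30, and then to 540 as a reserve against clinic dropout and uncertain estimates. The 540 is called tentative. Both the opening paragraph and the closing one say that the final size will be set from pilot or locally collected data.

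**The concern.** These are not two scenarios. The opening paragraph introduces the calculation that the later subsections carry out, with the same inflation factor, the same 20% loss and the same 540 infants. One calculation cannot have both a 20% and a 10% type II error rate.

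This would matter little if 540 were final. It is not. The pilot can update the SD, the intraclass correlation and the expected effect, but it cannot supply the power, which is a design choice to be fixed beforehand. Someone redoing the calculation from the opening paragraph would use 0.8; someone working from the formula would use 0.90. Leaving both in the text also allows the power to be settled after the pilot data are seen, to suit a convenient sample size.

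**Working it through.** **Inputs, all from the protocol**

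- Quantiles: 1.96 for two-sided 0.05; 1.28 for 90% power (Sample size formula). For 80% power the quantile is 0.84.
- Effect on the log scale: "For R = 0.25, 0.33, and 0.50, the corresponding Δ values are Δ = 0.26, 0.37, and 0.64". Leakage: "the ratio will be reduced in the control group by an amount equal to 10% of the reduction in the treated group".
- SDs: "we estimate the SD for log hair nicotine at σ = 1.00" and "we estimate the SD for log hair cotinine at σ = 1.15".
- Clustering: "Hence the IF is given by IF = 1+29*0.005 = 1.145".
- Response rate 0.8; equal numbers of clinics per arm; totals rounded up to the nearest 10.

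**Formulas.** The displayed equations could not be read in the copy used, so the standard forms are assumed:

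- Δ = ln[(1 − 0.1R)/(1 − R)]. This gives 0.2624, 0.3669 and 0.6419, which round to the printed 0.26, 0.37 and 0.64.
- Total N = 4(z_a + z_b)²σ²/Δ² × 1.145/0.8.

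**Reproducing the plan's figure.** For R = 0.33 and log hair nicotine at 90% power:

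- 4 × (1.96 + 1.28)² × 1.00²/0.3669² = 311.9
- 311.9 × 1.145/0.8 = 446.4, rounded up to 450, as printed.

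The same entry at 80% power:

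- 4 × (1.96 + 0.84)² × 1.00²/0.3669² = 232.9
- 232.9 × 1.145/0.8 = 333.4, rounded up to 340.

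**All six entries, with unrounded Δ**

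| Endpoint, R | Table 3 | 90% power | 80% power |
|---|---|---|---|
| Nicotine, 0.25 | 880 | 873.1 → 880 | 652.1 → 660 |
| Nicotine, 0.33 | 450 | 446.4 → 450 | 333.4 → 340 |
| Nicotine, 0.50 | 150 | 145.9 → 150 | 108.9 → 110 |
| Cotinine, 0.25 | 1,160 | 1154.7 → 1,160 | 862.3 → 870 |
| Cotinine, 0.33 | 600 | 590.4 → 600 | 440.9 → 450 |
| Cotinine, 0.50 | 200 | 192.9 → 200 | 144.1 → 150 |

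At 90% every entry matches its own cell; at 80% none does.

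**Sensitivity**

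- With the printed two-decimal Δ, 90% power gives 890/440/150 for nicotine and 1,180/590/200 for cotinine. Four entries then miss Table 3, by at most 10/450 = 2.2%. At 80% the same Δ values give 670/330/110 and 880/440/150, still far off.
- For nicotine at R = 0.33 and 80% power, taking R = 1/3 gives about 325. One-sided alpha gives about 258 to 263. Inflating by 1.2 instead of dividing by 0.8 gives about 313 to 322. None approaches 450.
- Using σ = 1.15 for nicotine at 80% gives the figures in the cotinine rows above, 870/450/150. Two of these coincide with the nicotine column, but 870 is not 880, the protocol states σ = 1.00 for nicotine, and the cotinine column would be left unexplained.

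**Size of the discrepancy**

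- (1.96 + 0.84)²/(1.96 + 1.28)² = 7.84/10.4976 = 0.747, so 80% power needs 25.3% fewer participants.
- In clinics of 30 with equal arms, 450 is 15 clinics, raised to 16 (480 infants). 340 is 11.3 clinics, raised to 12 (360 infants).
- The reserve inside 540 is therefore 540 − 480 = 60 infants against a 90% target, or 540 − 360 = 180 against an 80% target.

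**Power of the tentative size.** Effective number per arm at 540 is 540 × 0.8/1.145/2 = 188.6. With Δ = 0.3669 and σ = 1.00, the normal approximation gives 94.6% power. The corresponding figures are 90.2% at 450 and 91.9% at 480.

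**The case against.** The strongest reply is that nothing in the present design is too small. The opening paragraph understates the power that was used, so the error runs in the safe direction. Table 3, the steps from 450 to 480 to 540, and the 18 clinics all agree with the formula subsection, which gives the quantile, the power and the alpha together. A careful reader can work out which power was used. The 25% loss is also conditional: it arises only if 0.8 is carried into the recalculation with all other inputs unchanged, and the pilot may move the SD, the intraclass correlation, the effect size or even the choice of endpoint.

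Most of this stands. The shrinkage is a risk and not a forecast. The 540 is not itself the 90% result, which is 450; the rest is rounding to clinics and a reserve. The arithmetic also cannot show which power the authors intended, only which one they used.

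It does not remove the contradiction. The opening statement is as explicit as the later one, is the first that a reader meets, and misdescribes the calculation that follows. The 94.6% at 540 offers limited comfort, because the size is tentative and the increase over 480 was meant to absorb clinic dropout and poor estimates. How large that reserve is depends on which power is the target.

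**Conclusion.** The concern holds. The power of 0.8 in the opening paragraph is not the power behind Table 3; 90% is. On the stated inputs the design entry is 450 at 90% and would be 340 at 80%, with a type II error rate of 20% in place of 10%.

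This rests on the standard two-arm formula and the inferred expression for Δ, which return the printed Δ values and all six table entries. The 94.6% at 540 further assumes an intraclass correlation of 0.005, 80% response, no lost clinic and the normal approximation.

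The current tentative size is not short. The statement should nevertheless be corrected before the post-pilot recalculation, since that is the step it could mislead.

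**What to change.** In the opening paragraph of the Phase III sample size section, change the power to 0.90 so that it agrees with the formula subsection and Table 3. Add a sentence stating that the recalculation after the pilot will also use 90% power.

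If 80% is the real target, three changes are needed instead: correct the quantile and power in the formula subsection; recompute Table 3 (nicotine 660/340/110, cotinine 870/450/150); and restate how 540 is reached, since the reserve would then be 180 infants and not 60.

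The first option costs one corrected number and one added sentence, with no change to the design. The second reopens the justification of the sample size.

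### The target said to underlie the sample size (one third of the exposed-unexposed difference) is not the effect used to calculate it (a 33% cut in the exposed/unexposed ratio)

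*Protocol article*

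**What the plan says.** In the protocol article, assumption (a) under Sample size calculation for the Phase III trial sets a reduction in exposure as the "operative goal, on which sample size calculations were performed". It defines the change of substantive importance as "one third the difference in measured hair values between children exposed and unexposed to tobacco smoke". It names neither a scale for that difference nor the exposed group that serves as reference.

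Specification of the effect size starts from a different quantity, the "ratio of the hair nicotine or cotinine level between exposed and unexposed populations". It continues: "We assume that the program will reduce this ratio by 25%, 33%, or 50" (per cent). Leakage is added as follows: "the ratio will be reduced in the control group by an amount equal to 10% of the reduction in the treated group". It then states "We perform the calculations on a logarithmic scale" and reports that "the corresponding Δ values are Δ = 0.26, 0.37, and 0.64" for the three values of R.

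Under Hair Nicotine, Table 2 gives geometric means of 0.58 (no exposure), 2.63 (smoking outside the house) and 5.62 (smoking inside). The plan takes only the spread from this table: "we estimate the SD for log hair nicotine at σ = 1.00". Calculated Sample Size selects R = 0.33 and log hair nicotine, obtains 450, and raises it to 480 and then to a tentative 540.

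**The concern.** One third and 33% look like the same number, but they have different bases. With the unexposed level held fixed, reducing the ratio by 33% reduces the exposed level by 33% of itself. Reducing the exposed level by one third of its distance from the unexposed level is a smaller step on the raw scale, because part of the exposed level is background that is also present in unexposed children. On the log scale, one third of the distance is a larger step than a 33% cut.

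No mean from Table 2 enters Δ, so the target in assumption (a) never reaches the calculation. At stake is whether the sizing supports the property claimed for it, namely adequate power for the change the protocol calls substantively important. That property also governs how a null result would be read.

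**Working it through.** **Inputs.** z values 1.96 and 1.28 and division by a response rate of 0.8 (Sample size formula); inflation factor 1.145 (Estimation of the Inflation Factor); σ = 1.00 and the Table 2 geometric means (Hair Nicotine); leakage 10% (Specification of the effect size). The two displayed formulas are not present in the text at hand, so their form is inferred from the figures they must produce.

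**Step 1: reproduce the plan's figure.**

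N = 4(1.96 + 1.28)²σ²/Δ² × 1.145/0.8, with Δ = ln[(1 − 0.1R)/(1 − R)].

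With σ = 1.00 this is N = 60.1/Δ².

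- R = 0.25: Δ = 0.262, N = 873, rounded up to 880.
- R = 0.33: Δ = ln(0.967/0.67) = 0.367, N = 446, rounded up to 450.
- R = 0.50: Δ = 0.642, N = 146, rounded up to 150.

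These match Table 3, and the cotinine column also reproduces with σ = 1.15. The 450 therefore comes from the ratio rule at 90% power. At 80% power, R = 0.33 would need 334.

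**Step 2: express R = 0.33 as a share of the gap.** For an exposed level g and an unexposed level of 0.58:

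- Raw share = 0.33g/(g − 0.58). Inside: 0.33 × 5.62/5.04 = 37%. Outside: 0.33 × 2.63/2.05 = 42%.
- Log share = −ln(0.67)/ln(g/0.58). Inside: 0.400/2.271 = 18%. Outside: 0.400/1.512 = 26%.

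Neither is one third.

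**Step 3: size for one third of the difference, raw geometric means.** The cut in level is R = (g − 0.58)/(3g), put into the same Δ and N. The pooled row uses the geometric mean of the 127 inside and 69 outside children, 4.30. Power at 540 uses 540 × 0.8/1.145 = 377 effective children.

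| Exposed reference | R | Δ | N, 90% power | N, 80% power | Power at 540 |
|---|---|---|---|---|---|
| Inside (5.62) | 0.299 | 0.325 | 570 | 426 | 88% |
| Pooled (4.30) | 0.288 | 0.311 | 622 | 465 | 86% |
| Outside (2.63) | 0.260 | 0.275 | 797 | 596 | 76% |

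For comparison, at the Δ of 0.367 actually used, 540 gives about 95% power.

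**Step 4: size for one third of the difference, log scale.** The cut in level is R = 1 − (0.58/g)^(1/3): 0.53 inside, 0.49 pooled, 0.40 outside.

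- Leakage as 10% of the log change, so Δ = 0.9 × ln(g/0.58)/3: Δ = 0.681, 0.601 and 0.454; N = 129, 166 and 292.
- Leakage through the formula in Step 1: N = 122, 157 and 280.

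Power at 540 exceeds 99% in every case.

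**The case against.** The strongest objection is to the consequence. A reader might infer that the trial is underpowered for its own important difference. The documents do not support that as a general statement, for four reasons.

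- Assumption (a) fixes no scale. The endpoint is log hair nicotine and the calculations are done on logs. On that scale 540 is more than enough.
- The section containing assumption (a) states 80% power, while Sample size formula uses 90%. That conflict is a separate matter. Against 80%, 540 is adequate on raw geometric means for the inside and pooled references, and falls short only if every child resembles the outside-only group. The eligibility criteria require only that at least one parent smokes.
- Raw hair values could also mean arithmetic means. If lognormality is assumed with Table 2's own SDs, these are about 0.83 (unexposed), 10.9 (inside), 4.8 (outside) and 8.7 (pooled). The cuts become 30.8%, 27.6% and 30.2%, and 540 gives 91%, 82% and 89% power.
- The comparison that matters is with 540, not 450, because the increase was made partly to cover uncertainty in the estimates.

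All of this stands. Whether σ = 1.00 is the right SD is a different question and does not bear on this mismatch.

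It can also be said that the size is tentative and will be redone with pilot data. That is true, but it does not remove the point. Pilot data can update a mean or an SD; they cannot decide which of two definitions of the target applies. The recalculation is where the two definitions would diverge in practice.

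**Conclusion.** The point holds as an inconsistency in the stated basis of the sizing. The protocol says the calculation rests on one third of the exposed-unexposed difference, and it does not. On Table 2, 450 follows from that target on neither the raw nor the log scale.

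The size and sign of the discrepancy depend on the reading. On raw geometric means the target is a 26% to 30% cut, needing roughly 570 to 800 children at 90% power, so the calculated 450 is too small and 540 gives 76% to 88%. On the log scale the target is a 40% to 53% cut, needing roughly 120 to 290, so 540 is generous. An unqualified claim of underpowering is not justified.

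These figures assume σ = 1.00, the plan's inflation factor, response rate and 10% leakage, Table 2 geometric means as the levels, and the inferred formulas, which reproduce Table 3.

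**What to change.** State one target in both assumption (a) and Specification of the effect size, with its scale and its exposed reference group. Either route is sufficient:

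1. Align the definition with the calculation. Replace the one-third definition in assumption (a) with the effect used: a 33% reduction in geometric mean hair nicotine, a net log difference of 0.37 after 10% leakage. Add that on Table 2 this is 37% to 42% of the raw gap. Table 3 and the 540 stay as they are.
2. Align the calculation with the definition. Keep one third of the difference, choose the scale and reference group, derive R and Δ from Table 2, or from pilot data when available, and restate the power of 540. On raw geometric means R would be 0.26 to 0.30; on the log scale it would be 0.40 to 0.53.

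The first costs a sentence or two. The second costs one recalculation, and on the raw scale the restated power would be lower than at R = 0.33. In both cases say which power level the statement refers to, since the protocol gives both 80% and 90%.
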